### Data management

Data will be stored on a secure database. Participants will complete the outcome measures via an online link and will input their data directly into the database or complete paper copies and send via a provided stamped addressed envelope. Further details are available from the Chief Investigator. All interviews will be digitally recorded, anonymised, professionally transcribed verbatim and analysed using, if appropriate, NVivo8 software for data management.

### Statistical methods

#### Methods of analysis

Baseline demographics, type of IBD classification, Rome IV IBS criteria and baseline values of outcome variables will be presented for both study arms using descriptive statistics only.

The UK-IBDQ and global rating of symptom relief will be compared between the two study arms at 6 and 12 months after randomisation (analysis conducted after 12-month data collection point). The following covariates will be included in the model: baseline value of outcome measures, stratification factors, fatigue, pain and incontinence at baseline, age and gender. Facilitators will be added as a random effect in the intervention arm only.

Secondary outcomes will be analysed in the same way with inclusion of baseline value of respective outcome. Outcomes and covariates may change in the light of new information but will be agreed prior to unblinding of the data.

Pre-specified subgroup analyses to investigate subgroups who might respond better to treatment will be conducted as part of the process evaluation (see below).

A sensitivity analysis using imputation methods to allow for missing data and reasonable assumptions for those lost to follow-up will be carried out.

A detailed statistical analysis plan will be completed and signed off by the Programme Steering Group prior to unblinding of data.

## Economic evaluation methods

An economic evaluation using recommended methods [62] will be undertaken from the National Health Service /Personal Social Services and patients’ perspectives to evaluate the cost-effectiveness of the intervention at 12 months. The cost of the intervention, including facilitator’s contacts with each patient, website hosting and maintenance and facilitators’ training (venue, trainers’ and facilitators’ time, travel and subsistence, administrative support and materials) and supervision, will be evaluated.

Data on the use of health, social care and other services will be collected from all study participants using a study-specific IBD Resource Use questionnaire, developed within this Programme Grant, asking about contacts with primary and secondary care, investigations, medications, hospitalisations, employment and out-of-pocket expenses.

Unit costs will be sourced from national sources (e.g. Personal Social Services Research Unit: Unit Costs of Health and Social Care; Department of Health: NHS reference costs; British National Formulary; NHS Improvement: National tariff payment system) and will be applied to categories of resources used to estimate individual participant total costs. Health-related quality of life data will be collected using the EuroQoL EQ-5D-5L questionnaire.

We will follow the intention-to-treat principle, and missing data will be handled using multiple imputation approach. We will calculate quality-adjusted life years (QALYs) and total costs for each participant in the trial during the 12 months follow-up. We will evaluate the incremental QALYs and costs with allocation to the BOOST intervention and the intervention’s cost-effectiveness at 12 months follow-up. The costs and EQ-5D-5L utilities will be compared between the two study arms at 6 and 12 months after randomisation, with adjustments made for baseline values of outcome measures (costs in previous 3 months and EQ-5D-5L at baseline), stratification factors, fatigue, pain and urgency/incontinence at baseline, age and gender. Facilitators will be added as a random effect in the intervention arm only.

An incremental cost-effectiveness ratio (ICER) will be estimated as the additional cost per an additional QALY gained. Uncertainty around the ICER point estimate will be assessed [63]. The probability of the online IBD self-management intervention being cost-effective compared to usual care will be estimated at the NICE threshold values of £20,000 to £30,000 per QALY gained. One-way sensitivity analyses will be conducted to explore the uncertainty associated with the cost of the intervention and use of healthcare services.

A health economics analysis plan, specifying the health economics analyses in detail, will be finalised and signed off prior to unblinding of data.

## Methods: process evaluation

### Research question

What factors (promoters and blockers, individual and organisational) impact on the completion and effect of the intervention?

A mixed methods process evaluation of the RCT will be conducted based on the MRC guidance [64]. The design of the process evaluation is based upon the logic model and consequent discussion within the study team, so that the process evaluation can explore the areas of greatest uncertainty.

### Aims

To investigate the processes through which the intervention is delivered, and what is actually delivered in practice, to aid the interpretation of the results of the main trial and to inform future rollout and implementation of the intervention, if successful.

### Objectives of the process evaluation

Determine expectations at baseline through interviewsDetermine if the intervention was delivered as planned (intervention fidelity)Explore participant responses to the intervention both quantitatively (through routinely collected study process data) and qualitatively (through interviews)Explore participants’ responses to being in the control arm of the study through interviewsUnderstand IBD nurses’ views of the intervention and its integration and usability in everyday NHS care through interviewsConsider any potential contextual influences on the intervention implementation and outcomes.

Based on the logic model developed for the intervention, which provides a detailed description of the intervention and its causal assumptions, we will seek to monitor intervention fidelity and provide insights into how the intervention did or did not work in practice, any unintended consequences, as well as providing information to aid future implementation and dissemination. A list of key assumptions and uncertainties has been developed by the intervention development team. These will be explored and tested in this process evaluation.

The process evaluation will run concurrently with the RCT in a largely ‘passive’ model [64]. However, this passive model will not be operational during our internal pilot study and the teams will work closely together during the pilot to address any issues raised.

### Adherence

#### Fidelity to the protocol

Proportion of people randomised to the intervention who clicked on the link to the online intervention and commenced the intervention and completed a minimum of four online sessions will be considered to have adhered to the intervention. We will also assess the date the baseline CRF is completed, date ‘red flags’ were completed and the date randomised to check study processes worked as intended.

### Quantitative

Monitoring online log-ins (number and spacing/timing of log-ins and time spent on each section and in total): automatically collected by the programme software, enabling us to see how participants interact with the intervention.A record of number and time of facilitator telephone support sessions or emails.Evaluation of moderators and mediators of treatment effect section, below gives details of quantitative analysis of possible moderators and mediators of response to intervention.

### Qualitative

Fidelity to the intended facilitator support: a sub-set of facilitators’ messages will be analysed and compared with instructions in the training manual for fidelity to the intended facilitator support. All facilitator interactions online with participants will be captured and randomly selected interactions (messaging) will be stripped of all personal identifying data and subjected to content analysis [65], to enable assessment of intervention fidelity (as defined by the training day and intervention manual).Face-to-face, telephone or Skype interviews with a purposive sample of up to 30 recruits (or until apparent data saturation) before and after the intervention (attempting to recruit the same people before they know their group allocation and then the same people 6 months later; if it is not possible to recruit people for a second interview at 6 months (or when they drop out if this is sooner), these participants will be replaced by another participant who was allocated to the same group with broadly the same characteristics). Interviews will be completed at different times after recruitment, to understand expectations and experiences of the intervention, its acceptability and which aspects they felt were most or least helpful (informing adjustment to the intervention before future rollout), and for their opinions on changes in their cognitions and behaviours. We will also interview at least two thirds of the facilitators who are IBD nurse specialists (approx. 20: or until apparent data saturation) to understand their views on supporting the online intervention and fit with their existing workload.

Participants who have indicated on the trial consent form that they are happy to be approached about interviews will be purposively selected and consented for interviews. Facilitators indicating willingness will be interviewed. The topic guides for interviews have been developed with our PPI panel. Data will be analysed iteratively and as the interviews progress the topic guide will be adapted, based on themes which emerge from earlier interviews, to enable exploration of issues which appear relevant in later interviews.

The interview sample will be purposively selected to include both sexes, a range of ages, both IBD diagnoses and those who completed or did not complete (the intervention), or were in the CAU group to better understand patient perspectives on the intervention, experiences of being in a wait list control and whether this altered behaviours and cognitions around symptoms, whether non-completion was due to the design and demands of the intervention, or due to other factors.as well as any unanticipated pathways and consequences. For analysis, interpretive data analysis will be informed by the Analytical Hierarchy Framework (AHF) [65], guiding methods for handling, analysing and generating findings from qualitative data.

We will train patient volunteers to co-analyse anonymised qualitative data (as we have done successfully in other studies [4, 66–69]), and help us interpret and present our findings widely to patient and media audiences. NVivo software will be used to manage data and enable sorting, labelling and retrieval of data segments prior to the human endeavour of interpretation and representation of findings.

The process evaluation team will work to integrate these sources of qualitative and quantitative data into a coherent report which seeks to illuminate the results of the RCT. There will also be a mediation analysis (see above).

### Evaluation of moderators and mediators of treatment effects

The purpose of this additional quantitative process analysis is twofold:
To explore moderators of intervention effect

This will allow us to assess if there are any key subgroup effects and if the intervention should in future target specific groups of patients. For instance, if depression and disease activity moderate treatment effects, it may be best to focus the intervention on patients in remission and provide alternate treatment to people with depression. If medical treatment optimisation moderates outcome, then again this confirms best practice would be to provide optimised medical treatment before the intervention. Alternately, if there are no significant moderators of effects, the intervention may be generalisable to the broader IBD population.

Subgroup analyses to be investigated are those who underwent Optimise (stage 3); IBD in remission (see definition above); baseline measure of anxiety and depression (PHQ-9 and VSI); and ROME IV criteria for IBD met at baseline or not. These will be investigated by adding interactions terms to the analysis models used for the primary outcomes (UK- IBDQ and global symptom relief).
2.To explore mediators of change

Mediation analysis using structural equation models allows us to explore if a treatment effect occurs through hypothesised treatment mechanisms. We have based our choice of mediator measures on our cognitive behavioural model underpinning the intervention and described in our logic model (available on request form the lead author). Putative mediators have been mapped onto the key intervention components, i.e. the factors the intervention attempts to target to bring about improvements in symptom and quality of life. These include the following: the Visceral Sensitivity Index (VSI [56] and PHQ-9 [53] for symptoms of anxiety and depression; Self-efficacy for managing chronic disease 6-item scale [54]; Brief Illness Perception questionnaire [55]; All-or-nothing and avoidance/resting subscales from the Cognitive and Behavioural Responses to Symptoms questionnaire (CBRQ); IBD-Control [40]; faecal calprotectin [70]; satisfaction with outcome.

We are looking at whether proximal change in the mediators at 6 months predicts improvement in the outcomes at 12 months.

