## The IBD-BOOST programme of research

The current Randomised Controlled Trial (RCT) is stage 4 of IBD-BOOST, a UK National Institute for Health Research (NIHR) Programme Grant for Applied Research (PGfAR) funded programme (grant reference RP-PG-0216-20001). This programme aims to improve the quality of life of people with IBD by reducing the burden of IBD-related fatigue, abdominal pain and urgency/incontinence. Table 1 shows the four stages of the IBD-BOOST programme including this RCT.

**Table 1 Tab1:** The IBD-BOOST programme of studies on fatigue, pain and urgency in IBD

**Stage 1** of the programme involved focus groups and interviews with people with IBD and IBD nurse specialists. In line with MRC guidance, these data were used alongside a theory-and person-based approach to develop a digital cognitive behavioural self-management intervention (IBD-BOOST). This stage is now completed.	
**Stage 2** of the programme involves a large cross-sectional survey of people with IBD to investigate the inter-relationships of IBD-related fatigue, pain and urgency/incontinence symptoms and the proportions wanting support to manage these symptoms. This stage is in progress and is not described further here.	
**Stage 3** of the programme is a non-randomised experimental study to test the effectiveness of a checklist and algorithm for identifying and treating medical causes of these IBD-related symptoms. The medical abnormalities detected in the study will be treated. This stage is not part of the current RCT and is not described further here.	
**Stage 4** (the current study) is an RCT of online self-management for symptoms of IBD fatigue, pain and urgency/incontinence (IBD-BOOST), with an embedded pilot study, health economics evaluation and process evaluation. Potential participants will already have completed the IBD survey (stage 2). Some of them will also have participated in stage 3.	

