### Eligibility criteria

#### Inclusion criteria

Diagnosis of IBD (self-reported as having been medically diagnosed with IBD including patients with an ileo-anal pouch or stoma)18 years old or overLiving in England, Scotland or WalesHave participated in stage 2 of the programme (IBD-BOOST survey) and have self-scored one or more symptoms of fatigue, pain or urgency/incontinence as having an impact on their quality of life of 5 or more on a 0–10 scale when completing stage 2 (IBD-BOOST survey) or stage 3 (medical symptom optimisation) (whichever is the more recent)No ‘red flags’—see belowAccess to the online intervention via a computer or mobile device

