#### Sample size

Our primary outcome is the UK-IBDQ, range 0 to 120 where low values indicate poor quality of life. Using several published studies [47, 57, 58], we estimate the standard deviation of the change in score to be between 20 and 30. This would mean an effect size of 0.3 would equate to a difference of between 6 and 9 points on the scale. In the validation study [47], the difference in score between those with mild disease and disease in remission was 12 points and the effect of relapse was 10 points.

An effect size of 0.3 was observed in a small study of dietary advice in patients with ulcerative colitis [57].

We will randomise 680 patients, 340 in each group. Assuming a 20% loss to follow-up, there will be 270 in each group in the analysis. Assuming there are 30 facilitators, they will each support ~ 11 patients on average of whom ~ 9 will contribute to the analysis. If the ICC for clustering between facilitator is 0.04, the design effect will be 1 + 0.04 × 8 = 1.32 and the effective sample size in the intervention arm is 270/1.32 = 204. 270 in the control and 204 in the intervention arm would allow an effect size of 0.3 to be detected with 90% power.

A 20% drop-out assumption is based on drop-out rates from previous studies of self-management: 19.2% of 682 participants in IBD disease self-management (not online) [59]; 20.4% of 333 participants for online self-management of ulcerative colitis disease flares [33]; 18% control and 16% intervention of 1140 participants randomised for chronic disease self-management in other diseases [37].

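### The moderator section reads a non-randomised Optimise interaction as confirming best practice, and lack of significance in weak tests as support for generalisability

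*Protocol article*

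**What the plan says.** The section on evaluation of moderators and mediators plans interaction terms in the models for both primary outcomes. The candidate moderators are Optimise participation, remission, baseline PHQ-9 and VSI, and Rome IV status. It then says how results would be read. On Optimise: "If medical treatment optimisation moderates outcome, then again this confirms best practice would be to provide optimised medical treatment before the intervention". On the absence of findings: "if there are no significant moderators of effects, the intervention may be generalisable to the broader IBD population".

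Three other places bear on these readings:

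- Table 1 (The IBD-BOOST programme of research) says that stage 3 "is a non-randomised experimental study to test the effectiveness of a checklist and algorithm". Under Randomisation procedures, stage 3 participation appears only as a stratification factor.
- The inclusion criteria require a score of 5 or more on at least one symptom, taken "when completing stage 2 (IBD-BOOST survey) or stage 3 (medical symptom optimisation) (whichever is the more recent". The primary research question and the section on identifying participants add that these people want further help.
- The sample size section gives one power statement, for the main comparison: "270 in the control and 204 in the intervention arm would allow an effect size of 0.3 to be detected with 90% power". It gives no interaction size, subgroup share or power for any moderator.

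**The concern.** The first sentence draws a causal conclusion about treatment sequence from a contrast that randomisation does not protect. The trial randomises BOOST against care as usual. It does not randomise optimisation and does not compare orders of treatment. The sentence is unhedged, and it speaks only of moderation, so a smaller BOOST effect after optimisation would satisfy it as well as a larger one.

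The second sentence treats lack of significance as evidence that the effect is the same across subgroups, and then extends this to people with IBD in general.

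The section says that the analysis will help decide whether BOOST should target particular groups, and the dissemination plan lists a separate paper on mediators and moderators. If the sentences are followed as written, that paper could make a causal claim that rests on selection and a generalisability claim that rests on imprecision.

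**Working it through.** **1. What an Optimise interaction can show.** Within each Optimise stratum, BOOST versus care as usual is randomised and validly estimated. The interaction is the difference between those two effects, so it compares two populations formed without randomisation:

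- People who took part in stage 3 are screened on their symptom score after it. Those whose scores all fell below 5 are not eligible.
- People who did not take part in stage 3 are screened on the survey score. They include some whose symptoms would have fallen below 5 had they been optimised.

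The strata can therefore differ in persistence of symptoms, in whatever led people into stage 3, and in optimisation itself. The interaction cannot separate these.

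**2. The plan's own power figure.** Inputs from the sample size section: 340 per arm, 20% loss (340 × 0.8 = 272, taken as 270), design effect 1 + 0.04 × 8 = 1.32, so 270/1.32 = 204 effective in the intervention arm, and an effect of 0.3 SD. Alpha is not stated there; two-sided 0.05 is assumed.

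SE(main) = √(1/270 + 1/204) = 0.0928 SD. Power = Φ(0.3/0.0928 − 1.96) = Φ(1.27) = 89.9%. The stated 90% is reproduced, which supports the assumed alpha.

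**3. Precision of an interaction.** For a binary moderator with share p in both arms, the subgroup variances are V/p and V/(1−p), where V = SE(main)². Hence SE(int) = SE(main)/√(p(1−p)), and power = Φ(δ/SE(int) − 1.96). The protocol gives neither p nor δ. The main case takes δ = 0.3 SD, an interaction as large as the whole target effect.

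| Split | SE(int), 270/204 | 95% CI half-width | Power, δ = 0.3 | Power, δ = 0.3, no design effect (270/270) |
|---|---|---|---|---|
| 50:50 | 0.0928/0.5 = 0.186 | 0.36 SD | 36.6% | 41.4% |
| 20:80 | 0.0928/0.4 = 0.232 | 0.45 SD | 25.3% | 28.6% |
| 10:90 | 0.0928/0.3 = 0.309 | 0.61 SD | 16.1% | 18.0% |

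For other interaction sizes at 270/204, over splits from 20:80 to 50:50, power is 9.5% to 12.5% at 0.15 SD, 49% to 68% at 0.45 SD, and 73% to 90% at 0.6 SD. The interaction detectable with 80% power is 2.80 × SE(int): 0.52 SD at 50:50 and 0.65 SD at 20:80.

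**4. What a non-significant result leaves open.** A non-significant 95% interval contains zero. At 50:50 its full width is 2 × 0.36, so it must reach at least 0.36 SD on one side. With the protocol's SD of 20 to 30, that is 7.3 to 10.9 UK-IBDQ points, against a target of 6 to 9. Without the design effect the half-width is 0.34 SD, still above 0.3.

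**5. Who the result could apply to.** Everyone enrolled scored 5 or more on a symptom, and recruitment is among people asking for help. Even a precisely null interaction inside the trial would say little about people with IBD outside that group.

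**The case against.** The aim is labelled exploratory, the generalisability remark is hedged, and interaction terms in the primary models are the standard method. Optimise participation is a stratification factor, and research question 4 names the question and the expected direction (greater gains after optimisation). No primary estimate or test depends on either sentence. All of this is true. It means that the second sentence is a loose remark and not a decision rule. It does not rescue the first: the exploratory label does not soften a claim of confirmation, and a pre-specified direction does not remove selection into stage 3.

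A reader might infer three stronger things that the document does not support:

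- **That the moderator tests have 25% to 37% power as such.** That range depends on assumed alpha, interaction size and subgroup share. For a moderator that varies within a facilitator's caseload, the facilitator effect largely cancels and the figures are nearer 29% to 41%. PHQ-9 and VSI, if kept continuous, do not fit the binary formula.
- **That the tests would usually miss BOOST working in only one half of patients.** If the planned overall 0.3 SD came from one half, the effects would be 0.6 and 0, and power at 50:50 is about 90%. A high miss rate arises only if the overall effect is 0.15 SD, half of what the trial plans for.
- **That the section fixes a generalisability conclusion.** The wording says only that the intervention may be generalisable.

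**Conclusion.** The point holds on both sentences, more firmly on the first. A moderating effect of Optimise would be an association between stage 3 participation and the BOOST effect. It cannot confirm that optimisation should come first, and the sentence as written does not even require the effect to be larger after optimisation. This conclusion needs no numerical assumption.

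On the second sentence, inferring generalisability from non-significance is unsound at this sample size. Assuming two-sided alpha 0.05, a binary moderator, the planned effective 270 and 204, and an interaction of 0.3 SD, power is about 37% (50:50) to 25% (20:80), or about 41% to 29% without the design effect. The 95% CI half-width at 270/204 is at best about 0.36 SD on the plan's variance assumption. Covariate adjustment might narrow it, but the protocol gives no figure for that.

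Nothing here says whether optimising first is clinically right or wrong. The point is what these data could show.

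**What to change.** Make three changes in the section on moderators and mediators:

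1. Replace the claim about best practice with a statement that the Optimise interaction is exploratory, associational and hypothesis-generating, because stage 3 participation was not randomised and its participants were screened on symptoms after optimisation. State the direction being examined, in line with research question 4.
2. Commit to reporting every interaction estimate with its 95% CI.
3. Remove the step from non-significance to generalisability. Say instead that the data can neither establish nor exclude a subgroup difference within the reported interval.

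Two further steps may suggest themselves but are not recommended. A rule allowing a claim of consistency only when the interval excludes 0.3 SD in both directions could not be met with a half-width of 0.36 SD. A Holm correction over the interactions is debatable for exploratory moderators, and over ten tests its first step (alpha 0.005) would cut the 37% and 25% to about 12% and 6.5%.

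The change is to wording and reporting. It needs no new data and leaves the primary analysis untouched. The cost is more cautious claims in the moderator paper.
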